## Abstract

**Background:**

Major depression is a highly prevalent disorder causing severe personal distress, and high societal costs. Patients with depression often have comorbid insomnia disorder (ID) leading to even worse personal distress and worse treatment outcomes. Recent results from a non-randomised pilot study with internet-delivered Cognitive Behavioural Therapy (CBTi) for Insomnia (I-Sleep) added to regular depression care were promising regarding feasibility and initial effects on insomnia complaints and depression. However, no randomised controlled trial (RCT) has been performed yet to access the (cost-) effectiveness of I-Sleep for depression. Therefore, this protocol article presents the design of an RCT aimed to assess the (cost-) effectiveness of I-Sleep in addition to usual care for depression compared to usual care alone in depressed patients with a comorbid Insomnia Disorder (ID) treated at outpatient clinics for mood disorders.

**Methods /design:**

This is a multi-centre RCT with measurements at baseline and at 3, 6, 9, and 12 months of follow-up. Patients with depression and an ID are randomised to either I-Sleep treatment followed by regular depression care or to regular depression care alone. Our aim is to recruit one hundred and seventy-five patients from multiple outpatient clinics for mood disorders. The primary outcome is the change in depressive symptoms over 12 months of follow-up measured with the Patient Health Questionnaire (PHQ-9). Secondary outcomes are recovery from depression (PHQ-9), insomnia severity (Insomnia Severity Index, ISI), daily functioning (Work and Social Adjustment Scale, WSAS), general quality of life (EuroQol 5-level version, EQ-5D-5L), and societal costs (Adapted versions of the iMTA Productivity Cost Questionnaire, iPCQ and iMTA Medical Cost Questionnaire, iMCQ).

**Discussion:**

We hypothesize that the addition of I-Sleep to usual care will result in a significant improvement in depression treatment outcomes and quality of life as well as a decrease in healthcare and societal costs compared to usual care alone. This study is the first pragmatic RCT evaluating the effectiveness and cost-effectiveness of adding CBTi to usual care for depression.

**Trial registration:**

Netherlands Trial Register (NL8955). Registered on October 6^th^2020. https://trialsearch.who.int/Trial2.aspx?TrialID=NL8955

**Supplementary Information:**

The online version contains supplementary material available at 10.1186/s12888-022-04492-z.

## Background

Major depression is one of the most common mental disorders worldwide, with currently over 264 million people suffering from depression globally [1]. With a lifetime prevalence of 18.7% and a 12-month prevalence of 5.2% in the Netherlands, it is estimated that each year 546,500 people suffer from depression in the Netherlands [2]. Depression is associated with severe functional impairments, and high societal expenditures due to increased healthcare utilization and productivity losses [3–5]. In Europe, the total costs of major depression were estimated to be €92 billion in 2010, of which €38 billion concerning healthcare and patient costs, and €54 billion concern lost productivity costs [6].

Insomnia has a high prevalence as well with estimates for chronic insomnia ranging from 10 to 15% and for transient or occasional insomnia from 25 to 35% in the general adult population [7]. The societal consequences of insomnia are significant and include costs of insomnia treatments, increased health care utilization, decreased workplace productivity, and an increased accident risk [8].

Depression and insomnia often co-occur. It is estimated that of people with insomnia, 40% suffer from depression and that 80% of patients with depression also suffer from insomnia [9]. Moreover, patients with depression and insomnia have lower quality of life [10]. and worse treatment outcomes compared to patients with depression alone [11]. Furthermore, suicidal ideation is more common in this group than among patients with depression alone [11, 12]. Finally, patients who still experience insomnia after successful depression treatment are at higher risk of recurrent depression [13, 14].

Current guidelines for insomnia issued by the Dutch College of General Practitioners (Nederlands Huisartsen Genootschap, NHG) and the European Sleep Research Society recommend that treatment of insomnia should be primarily non-pharmacological, using cognitive behavioural therapy for insomnia (CBT-I) [15]. However, despite disadvantages, such as addiction and undesirable side effects, sleep medication is often prescribed to depressed outpatients with comorbid insomnia. This may be related to the belief held by therapists that symptoms of insomnia will disappear when depression is treated successfully. Another possible reason may be that therapists feel that they are no experts in the treatment of insomnia [16]. As a result, accessibility of CBTi may be limited due to a shortage of experienced therapists [9]. Thus, despite the negative effects of co-occurrence of insomnia and depression, insomnia is hardly ever specifically targeted with CBTi during the treatment for depression in a mental healthcare setting and as a result is often still present (in about 25% of patients) after treatment of depression [17].

Online CBTi has been shown to be effective in a large number of studies [18, 19]. Besides effectively improving insomnia related outcome measures, online CBTi also appears to reduce depressive symptom severity [20, 21]. Moreover, a recent study by Carney, (2017) showed that depression treatment alone can even worsen sleep symptoms [17].

I-Sleep is a guided online CBT intervention developed in the Netherlands that has been tested and found effective in various populations [9, 22, 23]. Recently, I-Sleep was adapted to serve as an add-on to usual care for depressive patients with comorbid insomnia treated in specialized mental healthcare [24]. This non-randomised pilot study by Dozeman, (2019) showed that the addition of I-Sleep to regular depression care resulted in a between-group standardized mean difference in sleep quality of 0.99 (*p* = 0.02) and in depressive symptoms 0.55 (*p* = 0.19) after treatment [24]. Furthermore, this pilot showed the feasibility of implementation of I-Sleep in a large mental healthcare outpatient clinic for mood disorders. Thus, adding I-Sleep to care as usual may improve outcomes in patients who are treated for depression while having comorbid insomnia. However, to date no study has yet examined the effectiveness of adding I-Sleep to regular depression care in a randomised controlled trial in a clinical mental health care setting in the Netherlands. Moreover, despite the profound economic burden associated with depression and insomnia, thus far, no study has assessed cost-effectiveness of adding I-Sleep to depression care as usual.

In this paper, we present the EINSTEIN study protocol (an acronym for: Effectiveness and cost-effectiveness of INternet-based treatment of insomnia in depressed patients Treated at a mental healthcarE outpatient cliINic). The EINSTEIN study is a randomised controlled trial with an economic evaluation alongside to evaluate the effectiveness and cost-effectiveness of adding I-Sleep to usual care for depression. We hypothesize that adding I-Sleep to regular depression treatment will be superior to usual care alone with regards to severity of depression and quality of life. Additionally, we expect that with improved treatment outcomes healthcare and societal costs decrease compared to usual care alone.

## Methods and design

### Study design and aims

This study is a pragmatic multi-centre, randomised controlled trial with an economic evaluation from both a societal and healthcare perspective. The overall objective of the study is to assess the effectiveness and cost-effectiveness of the internet-delivered CBTi treatment program I-Sleep as an addition to usual depression care alone over 12 months. Participants in this study are patients with both depression and insomnia disorder treated at an outpatient clinic for mood disorders in the Netherlands. Furthermore, a process evaluation of implementing I-Sleep in daily clinical practice will be conducted to assess the feasibility of I-Sleep as an integral component of depression treatment. The study protocol, recruitment materials, and measurement methods were approved by the Medical Ethics Committee of the VU University Medical Centre. This trial is conducted according to the principles of the declaration of Helsinki. Likewise, this trial adheres to the SPIRIT guidelines and methodology, see Additional file 1: Appendix A SPIRIT checklist.

### Recruitment

Patients are recruited within four mental health outpatient clinics for mood disorders throughout the Netherlands all offering e-Health interventions. Therapists and research assistants on-site are instructed to alert patients with depression and possible comorbid insomnia about the study. Patients who have shown interest in participating in scientific research during intake will be contacted by a research assistant and provided with further information concerning participation in the trial. Patients who consent are screened for eligibility by telephone. The presence of insomnia disorder will be assessed with a self-constructed questionnaire based on the DSM-5 criteria for insomnia disorder. Also, in addition to the clinical judgement of the psychologist at intake, items from the Mini International Neuropsychiatric Interview (MINI) will be administered to confirm the presence of unipolar depression. Eligible patients will be sent an information kit (including information about data storing and handling procedures) and an informed consent form by mail. When the signed informed consent form is returned to the research assistant on site, participants will be randomised into a treatment arm and will receive a link via email to complete the baseline measurement. After providing informed consent, participants can withdraw from the study at any time for any reason without consequences. For a more detailed account of patient flow in this trial see Fig. 1.

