### Randomization, blinding and treatment allocation

After inclusion, participants are randomly assigned to either the intervention group I-Sleep (before the start of the usual care) or the control group (usual care alone) on a 1:1 ratio. Variable block sizes are used. Randomization takes place at the patient level and is stratified by mental health outpatient clinics for mood disorders. An independent researcher has created an allocation scheme using a computerized random number generator (Castor). Randomization will be performed by another independent research assistant who reveals the randomization outcome. Due to the nature of the intervention, blinding of patients, therapists, researchers and research assistants was not possible.

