### Assessments

Measurements will be taken at baseline (T0) and at 3- (T1), 6- (T2), 9- (T3) and 12-month (T4) follow-up. All measures are completed online; participants will receive a link to the online questionnaires via email. Additionally, a randomly chosen selection of participants and therapists from all participating outpatient clinics for mood disorders will be invited for an in-depth interview by telephone as part of the RE-AIM process evaluation. Exit interviews will be held with participants who discontinue or deviate from intervention protocols. For a detailed overview of the measurements see Table 1.

**Table 1 Tab1:** Repeated measurements

Questionnaire	T0	T1	T2	T3	T4
Depression severity (PHQ-9)	x	x	x	x	x
Sleep quality (ISI)	x	x	x	x	x
Daily functioning (WSAS)	x	x	x	x	x
Quality of life (EQ-5D-5L)	x	x	x	x	x
Healthcare, patient and family costs (iMCQ)	x	x	x	x	x
Lost productivity costs (iPCQ)	x	x	x	x	x
Process evaluation questions	x	x			x

T0: baseline, T1: 3 months after T0, T2: 6 months after T0, T3: 9 months after T0, T4: 1 year after T0

Online measurements and instruments at different points of assessment. *PHQ-9* Patient Health Questionnaire-9, *ISI* Insomnia Severity Index, *WSAS* Work and Social Adjustment Scale, *EQ-5D-5L* EuroQol, *iMCQ* iMTA Medical Cost Questionnaire, *iPCQ* iMTA Productivity Cost Questionnaire, Process evaluation questionnaire according to RE-AIM framework adjusted to the EINSTEIN study

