### Primary outcome: depression severity

The primary outcome is the change in depressive symptoms during one year of follow-up. Depressive symptoms will be assessed with the web-based Patient Health Questionnaire-9 (PHQ-9) at baseline and at 3, 6, 9 and 12 months of follow-up. The PHQ-9 scores each of the nine DSM criteria on a scale from "0" (not at all) to "3" (nearly every day), resulting in a total score ranging between 0 and 27 which is divided into increasing severity categories resulting in the PHQ Depression Severity Index [29]. Recent studies show that the PHQ-9 delivered using web-based technology is a reliable instrument to assess the severity and frequency of depressive symptoms in the previous two-week period [30, 31]

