### Sample size

The sample size calculation is based on a previously conducted pilot study among depressive patients suffering from insomnia [24]. In this pilot study, the mean PHQ-9 score was 11.5 in the intervention condition (I-Sleep + usual care) and 15.0 in the control condition (usual care alone) at three months of follow-up. Assuming an SD of 7.1, an alpha of 0.05, and a power of 0.80, this results in a total required sample of 130. With four participating mental healthcare outpatient clinics for mood disorders and an Intraclass Correlation Coefficient (ICC) of 0.05, the total required sample size for the current trial is 140. Considering a dropout rate of 20% based on the pilot study, the required sample size is 175. This means all four mental healthcare outpatient clinics for mood disorders ought to include approximately 44 patients in total, i.e., 22 patients per year.

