### Primary outcome measures

To assess the difference in the improvement in depression symptom severity as assessed by the PHQ-9 over time between the I-Sleep group and usual care group, linear mixed models that account for the repeated measures within patients will be used. Three hierarchical levels will be included in the linear mixed models: mental healthcare outpatient clinic for mood disorders, patient and time. The primary effect is described by the coefficient of the time-treatment interaction term. If necessary, the analysis will be adjusted for confounders and/or stratified for effect modifiers.

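### The written order randomises participants before they complete the self-reported baseline, so knowing the allocation can influence the T0 PHQ-9 that anchors the primary interaction

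*Protocol article*

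**What the plan says.** The Recruitment section of the protocol article sets out a sequence: telephone screening, consent form by mail, signed form returned, and then "participants will be randomised into a treatment arm and will receive a link via email to complete the baseline measurement".

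The section on randomisation and blinding adds two facts. First, "Randomization will be performed by another independent research assistant who reveals the randomization outcome". Second, "Due to the nature of the intervention, blinding of patients, therapists, researchers and research assistants was not possible".

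Under Assessments, "All measures are completed online; participants will receive a link to the online questionnaires via email". Table 1 places the PHQ-9, ISI, WSAS, EQ-5D-5L and both cost questionnaires at T0.

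For the endpoint, "The primary outcome is the change in depressive symptoms during one year of follow-up", with the PHQ-9 taken at baseline and at 3, 6, 9 and 12 months. In the primary analysis, "The primary effect is described by the coefficient of the time-treatment interaction term".

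The text nowhere says that T0 must be submitted before randomisation, or that the allocation is withheld until it has been.

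**The concern.** A baseline is useful in a randomised trial because treatment assignment cannot have affected it. Here the written order puts assignment first, the assignment is disclosed, and the baseline is a subjective questionnaire that the patient fills in online. An arm difference at T0 may then be partly a reaction to the allocation as well as chance.

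The primary interaction measures change from T0, so a reaction confined to T0 appears as a treatment effect of the opposite sign. The ISI, WSAS, EQ-5D-5L and cost measures share the same T0. Participants can also be randomised without ever giving a baseline, and such gaps might differ between arms.

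The article itself reports preferences about allocation. Its Discussion says that patients find it hard to grasp that only half will get I-Sleep, and that some want regular depression care at once, which the I-Sleep arm cannot offer. Reactions in both arms are therefore plausible.

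**Working it through.** **1. The plan's own figure.** Inputs from the Sample size section: three-month PHQ-9 means of 11.5 and 15.0, so a difference of 3.5; SD 7.1; alpha 0.05 (taken as two-sided); power 0.80; allocation 1:1.

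n per arm = 2 × (1.960 + 0.842)² × (7.1 / 3.5)² = 64.6, rounded up to 65. The total is 130, as stated. The dropout step, 140 / (1 − 0.20) = 175, also reproduces. Neither figure depends on the order of baseline and randomisation. The 3.5 points serve below as a yardstick.

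**2. How a T0 shift reaches the interaction.** Let b be the arm difference (I-Sleep minus usual care) in mean T0 PHQ-9 caused by knowing the allocation. Let k be the fraction of that shift still present at every follow-up visit.

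- Categorical time: bias at each follow-up = k·b − b = −(1 − k)·b.
- Linear time: the least-squares slope weights for five equally spaced visits are −0.2, −0.1, 0, 0.1, 0.2. Bias per visit = −0.2·b + 0.2·k·b = −0.2·(1 − k)·b. Over four intervals (12 months) this is −0.8·(1 − k)·b.

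The largest bias arises when nothing persists (k = 0). If the shift persists fully (k = 1), it cancels.

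**3. Size at k = 0.** The documents give no value for b; these are assumptions.

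| b (points) | Categorical time | Share of 3.5 | Linear time, over 12 months |
|---|---|---|---|
| 0.5 | 0.5 | 14% | 0.4 |
| 1.0 | 1.0 | 29% | 0.8 |
| 1.5 | 1.5 | 43% | 1.2 |

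The 3.5 points are a three-month difference. The article gives no 12-month planning figure to set beside the last column.

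**4. Direction.** Lower PHQ-9 is better. If controls score worse at T0 from disappointment, or I-Sleep patients score better from hope, b is negative and the I-Sleep benefit is understated. If I-Sleep patients who wanted regular care at once score worse, b is positive and the benefit is overstated.

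**5. Illustration of error rates.** Assumptions: 70 evaluable per arm, SD 7.1, clustering ignored, one follow-up compared on change from baseline, no true effect, k = 0, and a baseline-to-follow-up correlation r of 0.3 to 0.7.

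SE = 7.1 × √(2(1 − r)) × √(2/70), which is 1.20 at r = 0.5. The two-sided rejection rate rises from 5% to about 6–8% for a shift of 0.5 and about 11–19% for a shift of 1. The excess rejections fall on the side to which the bias points.

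**6. Using T0 as a covariate.** The bias shrinks to about r × b, or 0.3 to 0.7 points for b = 1. It does not vanish.

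**The case against.** Several points on the other side have force.

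- **The order is not beyond doubt.** The sentence joins randomisation and the link with a plain conjunction, and the paragraph refers to the flowchart (Fig. 1) for detail. That figure was not available for this review. The text does not say when the patient learns the allocation relative to opening the link; that step is inferred. This stands, and it is why the fix includes a correction of the text if practice already differs.
- **Persistence and recall.** Patients remain unblinded, so part of a reporting shift may last and cancel. The article says the PHQ-9 covers the preceding two weeks, which may dampen a reaction to the news. The figures above are therefore upper limits for the assumed b.
- **Direction.** A reader might infer a risk of falsely claiming efficacy. The most obvious mechanisms, disappointment in controls and hope in the I-Sleep arm, point the other way. The Discussion gives one reason for the opposite sign, so the direction remains open.

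Two stronger readings are tempting, and the documents do not support them:

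- **Sleep-medication subgroup.** A reader might infer that this subgroup is defined on post-randomisation data. The article does not say how sleep medication at baseline is ascertained; it could come from intake or patient records.
- **Intention-to-treat.** A reader might infer that the principle is undermined. A linear mixed model can use T1–T4 from a patient who has no T0, so a missing baseline does not by itself remove anyone. What remains is a possible difference between arms in missing T0.

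Screening and consent precede randomisation, so the stated order does not compromise selection into the arms.

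**Conclusion.** The point holds. As written, randomisation comes before the e-mailed, self-reported baseline, the allocation is disclosed, and the text states no safeguard. This is a procedural order that the article itself fixes, so it is not a detail left to an analysis plan.

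The primary interaction can be biased by up to b with categorical time, or about 0.8 × b over 12 months with linear time, to the extent that the T0 shift does not persist. For an assumed b of 0.5 to 1.5 points this is at most 14% to 43% of the planning difference with categorical time. The size of b is unknown and its sign uncertain. The conclusion also assumes that patients learn their arm before completing T0, which the text implies without stating it, and that Fig. 1 does not show another order.

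**What to change.** - **Order.** State in the Recruitment section, and enforce in the data-capture system, that T0 must be submitted before randomisation and before the allocation is revealed. If this is already the practice, correct the Recruitment text to say so.
- **Patients already enrolled.** Record for each whether T0 was completed before or after the reveal.
- **Sensitivity analysis.** Compare PHQ-9 between arms at T1–T4 without T0 as outcome or covariate. This removes the T0 problem, though not any reporting effect at follow-up in an unblinded trial. The figure of 130 reproduces from a comparison of three-month means with SD 7.1 and no baseline term, so a contrast at that visit is the one the trial was sized on.

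The cost is a short amendment and one workflow rule. A few consented patients who never complete T0 will not be randomised. The required sample size does not change. The Trial status section reports that inclusion was still open when the article was submitted, so later participants could be protected; if recruitment has since closed, only the recording and the sensitivity analysis remain.

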**Fig. 1 Fig1:**
[figure not shown]
Flowchart of the EINSTEIN study design

### Inclusion and exclusion criteria

In order to be eligible to participate in this study, patients should be between 18 to 75 years old and diagnosed with unipolar major depressive disorder according to the DSM-5 [25] criteria during intake and should be scheduled for treatment for depressive disorder at one of the participating mental healthcare outpatient clinics. In addition, all patients must fulfil the DSM-5 criteria for an insomnia disorder [25] during the telephone screening. Exclusion criteria are, insufficient command of the Dutch language (I-Sleep is only available in Dutch) working night shifts, sleep-related disorders other than insomnia (e.g., sleep apnoea) previously diagnosed by a physician or other (mental) health care specialist, no daily access to an internet-connected computer and the presence of a mental health crisis. Other comorbid mental disorders or somatic diseases are allowed if they do not provide a sufficient explanation for the existence of insomnia complaints. The use of antidepressant medication and sleep medication is allowed in both treatment arms. All in- and exclusion criteria are assessed during a screening procedure performed by telephone by the research assistant on-site using items from the MINI Diagnostic Interview [26] and a DSM-5 insomnia criteria-based screener designed for this study.

